## Abstract

**Background:** Infection contributes to significant morbidity and mortality particularly in the very young and in low- and middle-income countries. While vaccines are a highly cost-effective tool against infectious disease little is known regarding the cellular and molecular pathways by which vaccines induce protection at an early age. Immunity is distinct in early life and greater precision is required in our understanding of mechanisms of early life protection to inform development of new pediatric vaccines.

**Methods and Analysis:** We will apply transcriptomic, proteomic, metabolomic, multiplex cytokine/chemokine, adenosine deaminase, and flow cytometry immune cell phenotyping to delineate early cellular and molecular signatures that correspond to vaccine immunogenicity. This approach will be applied to a neonatal cohort in The Gambia (*N* ~ 720) receiving at birth: (1) Hepatitis B (HepB) vaccine alone, (2) Bacille Calmette Guerin (BCG) vaccine alone, or (3) HepB and BCG vaccines, (4) HepB and BCG vaccines delayed till day 10 at the latest. Each study participant will have a baseline peripheral blood sample drawn at DOL0 and a second blood sample at DOL1,−3, or−7 as well as late timepoints to assess HepB vaccine immunogenicity. Blood will be fractionated via a “small sample big data” standard operating procedure that enables multiple downstream systems biology assays. We will apply both univariate and multivariate frameworks and multi-OMIC data integration to identify features associated with anti-Hepatitis B (anti-HB) titer, an established correlate of protection. Cord blood sample collection from a subset of participants will enable human *in vitro* modeling to test mechanistic hypotheses identified *in silico* regarding vaccine action. Maternal anti-HB titer and the infant microbiome will also be correlated with our findings which will be validated in a smaller cohort in Papua New Guinea (*N* ~ 80).

**Ethics and Dissemination:** The study has been approved by The Gambia Government/MRCG Joint Ethics Committee and The Boston Children's Hospital Institutional Review Board. Ethics review is ongoing with the Papua New Guinea Medical Research Advisory Committee. All de-identified data will be uploaded to public repositories following submission of study output for publication. Feedback meetings will be organized to disseminate output to the study communities.

**Clinical Trial Registration**: Clinicaltrials.gov Registration Number: NCT03246230

## Background and Rationale for the Study

Infection remains a major cause of morbidity and mortality accounting for over 30% of global deaths occurring each year in children under the age of 5 years (1). The burden of infectious disease is highest among the very young and in low- and middle-income countries (1, 2). In 2017, 5.4 million deaths occurred in children under the age of five accounting for 38.9 deaths per thousand live births (2). Roughly 2.5 million (47%) of these under five deaths occurred in the first 28 days of life (1). The leading causes of under-five mortality in 2016 were complications of prematurity (18%), pneumonia (16%) intrapartum related events (12%), congenital anomalies (9%), diarrhea (8%), neonatal sepsis (7%), and malaria (5%) (1). Thus, infectious disease remains a leading cause of mortality and indeed morbidity during the most vulnerable period of life.

Immunization is a powerful and highly cost-effective approach to prevent infection (3–5). It is estimated that for every public dollar spent on immunization, there is a $44 return on investment (6), and that vaccines have contributed to saving over 20 million lives and $350 billion between 2001 and 2017 in 73 low and middle income countries alone (6). Vaccines are thought to save 2–3 million lives each year worldwide (7) and have contributed to disease eradication (8–10) with prospects for eradicating another disease in sight (11–13). However, there are few vaccines specifically licensed for use at the extremes of age partly because little is known regarding the molecular pathways by which vaccines induce protection, particularly in the “developing” immune system of the very young (14).

Systems biology, is a powerful approach to gain deep insight into biology and has increasingly been applied to vaccinology to obtain insights into vaccine protection (15). However, these powerful techniques have not been applied to the most vulnerable: newborns in resource poor settings (16). To meet this need, an international group of academic biomedical centers have partnered to form the Expanded Program on Immunization Consortium (EPIC) (Figure 1) partnering to utilize systems biology to unravel the complex relationships between vaccine immunogenicity via early, vaccine-induced transcriptomic, metabolomic, proteomic, multiplex cytokine/chemokine, adenosine deaminase and immune cell phenotype (“OMIC”) signatures. With funding from the United States National Institute of Health (NIH), through National Institute of Allergy and Infectious Diseases (NIAID) U19 Initiative for the Human Immune Project Consortium (HIPC), the study described below will be conducted to explore these complex relationships.

**Figure 1 F1:**
[figure not shown]
Geographical distribution of partnering sites for the EPIC-002 study. An overarching administrative core, clinical core (CC), data management core (DMC), as well as an *in vitro* vaccine modeling project are based at Boston Children's Hospital (Boston, MA). Clinical Core Sites are located in The Gambia (West Africa) and Papua New Guinea (Australasia). End-point assays are conducted in The Gambia (whole blood assay and cell mediated immunity), PNG (whole blood assay), University of British Columbia (flow cytometry and RNASeq), BCH (multiplex cytokines/chemokines, plasma proteomics, *in vitro* modeling including WBA and tissue constructs) as well as the Center for Vaccinology (CEVAC; Ghent, Belgium; anti-hepatitis B surface antigen titres).

Previous EPIC pilot studies (EPIC-001) conducted at the Medical Research Council Unit The Gambia at London School of Hygiene and Tropical Medicine (MRCUG at LSHTM) and the Papua New Guinea Institute of Medical Research (PNGIMR) between 2015 and 2017 demonstrated the feasibility of measuring robust and cogent “OMIC” readouts from small volume blood samples to obtain “OMIC” signatures (17). Based on the pilot data, the current EPIC research project will focus on the immunogenicity of Hepatitis B (HepB) vaccine for which a clear correlate of protection exists (i.e., anti-hepatitis B surface antigen antibody (Ab) titres) (18, 19). Cell mediated immunity (CMI) though not validated as a correlate of protection but which appears to play a role in long-term immunity (post-primary series titres of 10 mIU/ml or greater have been shown to correlate with the induction of memory T helper-and B-cell responses) (20), will also be assessed. In addition, we will examine if concomitant vaccination with Bacille Calmette Guérin (BCG) can modulate the response to HepB vaccine. Both vaccines are recommended for routine use at birth in these countries and in similar settings.

The HepB vaccine is safe, immunogenic and highly effective and is on the list of Expanded Programme on Immunization (EPI) recommended childhood vaccines. The first dose is recommended on the day of birth to prevent vertical and horizontal transmission of Hepatitis B virus (HBV) (18). The HepB vaccine has one of the best-characterized serologic correlates of protection (CoP), and is the only clear CoP for any neonatal vaccine (18). First described in The Gambia, this CoP is the lower limit of the peak Ab response measured >1 month after the primary series (3 or 4 doses), defined as an anti-Hepatitis B surface antigen (anti-HBs) Ab level of >10 mIU/mL (18, 19). Importantly, while an anti-HBs threshold of >10 mIU/ml represents the minimal level for protection from infection, a relationship exists in direct quantitative correlation between Ab level and duration of protection (i.e., the higher the anti-HBs titer the better and longer protection) (19). In addition, there is evidence to suggest that the higher the titer after the first dose of HepB vaccine, the higher the titer after the last dose, and persistence (18, 19). This implies that variability in response to the first dose (21) of HepB vaccine may predict long-term immunogenicity (18). Substantial quantitative inter-participant variation in absolute anti-HBs levels are the norm after each dose of HepB vaccine as with many other vaccines. Such inter-participant variability represents a key ingredient for meaningful analyses using a systems vaccinology approach (21).

The neonatal HepB vaccine immune response has been reported to be altered by co-administration of BCG, which is co-administered as part of the standard EPI, and likely to perturb the immune response to HepB vaccine *in vivo* (22, 23). Maternal antibodies to HepB have also been documented to impair the post vaccination immune response to HepB vaccine in newborns (18, 24, 25). The mechanisms that underlie HepB vaccine-induced immunogenicity in newborns, including Ab and CMI, are incompletely characterized particularly as it relates to variations in response.

Given the many advantages, HepB vaccine represents an ideal model in which to decipher what governs immunogenicity in early life. Similar reasoning regarding HepB vaccine as a model for systems biology have led to deciphering of mechanisms relevant for the immune response in older adults (26). This project will study the systems biology responses of newborns receiving HepB vaccination with and without concomitant BCG vaccine compared to a group of infants receiving both vaccines later in the first week of life to allow us to observe any changes occurring over the first week of life as a result of immune ontogeny rather than induced by vaccination. *In vitro* tissue constructs will also be set up to model the *in vivo* responses and maternal antibodies will be assayed to enable correlation with the infant responses.

The ability to show a correlation between age-specific molecular patterns (“signatures”) and vaccine-mediated protection (our main outcome measure) should accelerate the development and optimization of vaccines against childhood infections of major global health importance.

## Study Questions, Objectives

The overall goal of the project is the characterization of vaccine-specific “OMIC” signatures that correlate with vaccine-type specific immunogenicity in human newborns.

The EPIC-002 study will characterize vaccine-induced “OMIC” signatures and their relationship to HepB vaccine CoP and characterization of the impact of BCG and maternal antibodies (MatAbs), thereby informing development of vaccines optimized for early life immunization.

Specific Objectives:

Measure adaptive immune responses to HepB vaccine, enabling correlation of *in vivo* “OMIC” signatures and *in vitro* vaccine Modeling assays with established correlates of protection.Characterize the pre-vaccine “OMIC” and immune *in vivo* signatures that may predict immunogenicity of HepB vaccine in human newborns.Characterize the impact of HepB vaccine with or without BCG on neonatal “OMIC” and immune *in vivo* signatures that predict immunogenicity of HepB vaccine.Measure maternal antibodies (MatAbs) to HBV in relation to vaccine-induced neonatal and infant “OMIC” vaccine signatures and adaptive responses.Interrogate functional correlations identified *in silico* using novel human *in vitro* platforms.Validate identified “OMIC” signatures in a distinct and independent newborn cohort recruited from Papua New Guinea (PNG).

## Study Design

The program consists of two neonatal cohort studies. A longitudinal neonatal cohort study will be conducted in The Gambia with a total follow-up time of roughly 5 months that serves as the program's core study. Following completion and analysis of The Gambian study, a validation cohort study will be conducted in Papua New Guinea to validate the key findings of the Gambian study. The two studies will harmonize procedures and protocols.

Participants will be recruited within the first 24 h of life into one of four broad groups as detailed below to receive either HepB vaccine alone, BCG vaccine alone or both HepB and BCG vaccines at this time point. The fourth group will have the birth doses of vaccines deferred till a time point within the first week of life. All infants will receive the recommended birth dose of polio vaccine a maximum of 10 days post-vaccination depending on the group assignment.

Two mL of venous blood will be drawn from each participant at the point of recruitment to assess “OMIC” responses. Each participant will have a maximum of two blood draws within the first week of life. In the core cohort in The Gambia, infants will be randomized into three subgroups that will have the second blood sample collected at 1, 3, or 7 days following the initial sampling. The cohort in The Gambia therefore consists of 12 different groups (Table 1). For the PNG cohort, all infants will have the second blood draw on the same day of life: analysis of The Gambia cohort will inform whether this will be at day 1, 3, or 7 of life. Subsequent visits and blood draws are as detailed in the Clinical Cohort Table below (Table 1)

**Table 1 T1:**
[figure not shown]
Clinical cohort table for infants recruited in The Gambia (discovery cohort) and Papua New Guinea (validation cohort).

*Table courtesy [name], Boston Children's Hospital*.

*In vitro* effects of the HepB vaccine and BCG vaccines will be studied in two *in vitro* assays using blood derived from the same study participants immunized *in vivo*: (a) whole blood assay (WBA) run at the recruitment sites on the day of sample collection and (b) in three-dimensional microphysiologic tissue constructs employing cryopreserved cord blood-derived mononuclear cells and plasma (27), enabling *in vitro* mechanistic interrogation of cellular and molecular signatures that correlate with anti-HepBsAg (anti-Hepatitis B surface antigen) titres *in vivo*.

Blood samples and rectal swabs for epigenetic and microbiome analysis will be collected and stored from participants in The Gambia. Maternal blood samples to enable correlation of maternal anti-HB Abs to infant responses will also be collected.

## Study Analysis Plan

This study aim is to identify “OMIC” signatures that correlate with HepB vaccine responses, as assessed by anti-HB titer (a well-established CoP), by leveraging both pre- and post-vaccine transcriptomic, proteomic, metabolomic, and cellular profiles. Our intention is to apply both univariate and multivariate frameworks to identify either a ranked list of molecular features associated with anti-HB titer or subsets of the molecular features best able to predict anti-HB titer, respectively. We plan to derive signatures in three distinct groups of newborns (corresponding to the distinct vaccination schedules) and compare across groups to gain a better understanding of the molecular basis of adjuvantation of HepB vaccine with BCG (given before, after or simultaneously). We further plan to derive robust multi-“OMIC” signatures correlating with effective HepB immunization by integrating across all available “OMIC” datasets. These signatures will then be validated in a distinct and independent newborn cohort recruited from PNG. Finally, the correlations identified by these various *in silico* analyses will be tested using the novel human *in vitro* platforms.

We will apply these methods to define baseline cellular and molecular pathways/hubs/nodes that predict vaccine immunogenicity and assess specific signatures *in vitro* that provide insight into vaccine mechanisms of action (MOA).

## Sample Size/Biostatistical Considerations

The cohort design included careful consideration of statistical power and sample size. Power calculations in the setting of traditional OMIC designs are well-documented (28) and we performed power calculations for OMIC platforms or flow cytometry based on preliminary data (unpublished data). Although we intended our tests of hypothesis to borrow strength across data types, little has been published on statistical power for integrative analyses or cross-platform comparisons, so this characteristic of our design was not taken into account when determining sample size. Power calculations were carried out using group sizes ranging between *n* = 30 or *n* = 60 per group, two-sided significance criterion (alpha) of 0.05, and a target 80% power to detect.

Since preliminary data for flow cytometry were not available, we performed a worst-case power analysis using a real-world published data on the most variable cell subpopulation where a significant difference was still identified comparing healthy, immunosuppressed, and transplant-tolerant individuals (29). This provided a lower bound of the minimum sample size required to detect a significant difference in cell sub-populations that could act as potential biomarkers. We found *n* = 30 would result in 80% power to detect a 2.3-fold difference in the relative abundance of a cell population, while *n* = 60 would result in 80% power to detect 1.8-fold difference, assuming a balanced design.

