### OMIC Analyses

We considered power to detect correlations between biomarker signals of any type and the CoP. We assumed approximate normality, after data transformation (e.g., log-transformation) and calculated detectable Pearson coefficients for samples using group size *n* = 30 or *n* = 60. We concluded that our design offered 80% power to detect correlations between continuous measures as small as *r* = 0.25–0.48. Additional parameters were included when carrying out power calculations for the transcriptomic analysis to account for variable coverage [e.g., read depth across biosamples using RNASeqPower v1.10 (28)]. Here we considered power to detect differentially abundant transcripts between two groups and estimated within-group standard deviation from preliminary data, as before. We found *n* = 30 would result in 80% power to detect a 2.4-fold difference in the relative abundance of a transcript, while *n* = 60 would result in 80% power to detect 1.4-fold difference, assuming a balanced design.

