## Randomization and Blinding

Following assessment of eligibility by the study physician, newborns will be randomly assigned to 1 of 12 groups in The Gambia (60 per group), and 1 of 4 groups in PNG (20 per group), using a computer-generated block randomization sequence. In The Gambia, the code will allow block randomization of 720 study participants into 12 groups, using random block sizes of 24 and 48. In PNG, block sizes of 8 will be used. Each study participant will be assigned sequential identification numbers (IDs) starting from 001 to 720 for The Gambia, and 1,001–1,080 in PNG. A check digit character will be augmented to each of these numbers to make up the participant IDs which will be generated using the Damm algorithm (https://en.wikipedia.org/wiki/Damm_algorithm; date accessed 08 November 2016). Here the check digit numbers 0–9 will be converted to letters A-H and J-K. The IDs for the Gambian cohort will be prefixed with the letter “G” which stands for Gambia. The randomization code will use the web application developed by the Statistics and Bioinformatics department at MRCG to generate the IDs including the check digit and prefix as detailed above (the app is available on https://stats.mrc.gm/chkdgt-id/). Randomization code for the PNG cohort will be generated at BCH using similar methods. Randomization groups will be printed on cards labeled with the participant identification number and allocated in the sequence in which the infants will be recruited. Cards will be sequentially allocated by clinical staff as participants are screened.

Due to the nature of randomized groups and difficulty of blinding to randomized vaccine groups, staff in direct contact with participants will be unblinded, while all laboratory staff at the sites will be blinded to participants assigned group throughout the study.

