##### Epigenetics

To compare differential gene methylation patterns (epigenetics) following vaccination genome-wide changes in the epigenome will be assessed via the Infinitum Methylation EPIC bead array. The analytical laboratory for this assay is yet to be determined.

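### The stated detectable effects are those of one unadjusted test at alpha 0.05, not of the OMIC-wide feature screen that the plan describes

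*Protocol article*

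**What the plan says.** In the protocol article, Sample Size/Biostatistical Considerations gives one criterion for all power calculations: "two-sided significance criterion (alpha) of 0.05, and a target 80% power to detect", with "group sizes ranging between *n* = 30 or *n* = 60 per group". From this come detectable differences in a cell population of 2.3-fold (n = 30) and 1.8-fold (n = 60).

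OMIC Analyses concludes that the design has "80% power to detect correlations between continuous measures as small as *r* = 0.25–0.48". For RNA sequencing it says "Here we considered power to detect differentially abundant transcripts between two groups" and gives 2.4-fold at n = 30 and 1.4-fold at n = 60. Read depth and a within-group standard deviation enter that calculation. No adjusted threshold, FDR target or feature count does.

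The Study Analysis Plan sets the task these figures are meant to support: to "identify either a ranked list of molecular features associated with anti-HB titer or subsets of the molecular features best able to predict anti-HB titer". It draws on transcriptomic, proteomic, metabolomic and cellular profiles, before and after vaccination, in three vaccine-schedule groups. Under Randomization and Blinding, "newborns will be randomly assigned to 1 of 12 groups in The Gambia (60 per group".

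**The concern.** A power figure holds for the threshold at which it was computed. Here the threshold is that of a single test, while the planned analysis ranks very many features per platform and repeats this across groups and sampling days. If features are called under FDR control and true signals are sparse, the working per-test threshold lies well below 0.05, and the stated effects no longer have 80% power.

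The discovery hits decide what is carried to the Papua New Guinea cohort (80 infants, 20 per group) and to the in vitro models. Validation there can remove false hits, but it cannot recover features missed in The Gambia. If realistic sensitivity is not stated, a short hit list could be misread as an absence of biology.

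**Working it through.** **Inputs from the protocol article.** Two-sided alpha 0.05; 80% power; n = 30 or 60; r = 0.25–0.48; transcript folds 2.4 (n = 30) and 1.4 (n = 60); 60 infants in each of 12 groups, so 3 × 60 = 180 per vaccine schedule before any loss to follow-up.

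**Assumptions, not in the document.** FDR q = 5%; share of truly associated features π = 1%, 5%, 10% or 20%.

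**1. Reproduce the stated correlation.** By Fisher z, r = tanh((1.960 + 0.842)/√(n − 3)).
- n = 30: tanh(2.802/5.196) = 0.49. A noncentral t calculation gives 0.47. Power for r = 0.48 is Φ(0.523 × 5.196 − 1.960) = 78%. The upper end of the stated range is therefore a single unadjusted test.
- n = 60: tanh(2.802/7.550) = 0.355. The lower end, 0.25, does not reproduce at n = 60: it has 49% power there and needs n of about 123. That is a separate problem. Below, the n = 60 reference is the recomputed 0.355.

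**2. Working per-test alpha under FDR control.** α* = q·π·0.8 / ((1 − q)(1 − π)). For π = 1%: 0.0004/0.9405 = 0.00043.

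**3. Detectable r at α\*.** Replace 1.960 by the normal quantile for α*. For π = 10% and n = 60: tanh((2.828 + 0.842)/7.550) = 0.451.

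**4. Detectable transcript fold at α\*.** The log fold scales by k = (z for α* + 0.842)/2.802. For π = 10%: k = 3.670/2.802 = 1.31, so 1.4^1.31 = 1.55 and 2.4^1.31 = 3.15. Each stated fold is scaled on its own, because the pair does not fit one standard deviation: 2.4-fold at n = 30 would imply 1.86-fold at n = 60.

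| π | α* | r, n = 30 | r, n = 60 | r, n = 180 | fold, n = 30 | fold, n = 60 | power, r = 0.48, n = 30 |
|---|---|---|---|---|---|---|---|
| single test | 0.05 | 0.49 | 0.355 | 0.21 | 2.4 (stated) | 1.4 (stated) | 78% |
| 1% | 0.00043 | 0.69 | 0.52 | 0.32 | 3.91 | 1.69 | 21% |
| 5% | 0.0022 | 0.64 | 0.475 | 0.285 | 3.38 | 1.60 | 37% |
| 10% | 0.0047 | 0.61 | 0.45 | 0.27 | 3.15 | 1.55 | 46% |
| 20% | 0.0105 | 0.575 | 0.42 | 0.25 | 2.89 | 1.50 | 56% |

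**5. When is 0.05 enough?** Setting α* = 0.05 gives π/(1 − π) = 0.05(1 − q)/(0.8q).
- q = 5%: 1.1875, so π = 54%.
- q = 10%: 0.5625, so π = 36%.
- q = 20%: 0.25, so π = 20%.

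**6. Expected false share if features were called at 0.05 with 80% power.** 0.05(1 − π)/(0.05(1 − π) + 0.8π) gives 86%, 54%, 36% and 20% for π = 1%, 5%, 10% and 20%.

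The cell-population folds (2.3 and 1.8) are not rescaled: the number of populations screened is not given, so the size of their penalty is unknown.

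**The case against.** The strongest reply is that nothing here is concealed and much is exploratory. The article states its alpha openly and says that borrowing strength across data types was not counted. A ranked list is not a list of features called at 0.05, and the multivariate and integrative analyses are not a series of single tests. The flow cytometry figure is presented as a worst case. The error control for the analysis may sit in a statistical analysis plan that is not shown, so its absence from a condensed article is no fault. All of this stands. It limits the point to the power statement, but does not make a single-test figure the power of the screen.

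Three stronger readings are tempting and not supported.

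- A reader might infer that the stated effects fail under every form of false discovery control. FDR control is adaptive, and step 5 shows combinations at which 0.05 suffices.
- A reader might infer that the feature lists would be mostly false. That assumes calling at 0.05, which the article does not say. Even then the false share is 36% at 10% true features.
- A reader might infer that the study cannot detect the effects it was sized on. DOL0 is sampled in every infant, so baseline features can use 180 infants per schedule, and the detectable r of 0.32–0.27 then lies inside the stated range. The loss applies to post-vaccine features tied to one sampling day, where n stays at 60.

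The genome-wide methylation work ("genome-wide changes in the epigenome will be assessed") adds little: it is not among the profiles listed in the Study Analysis Plan, and no power is claimed for it.

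**Conclusion.** The point holds in limited form. The detectable effects in the sample-size text belong to one unadjusted two-sided test. They are not 80%-power effects for the planned screen unless a large share of features is truly associated, and the document gives no support for such a share.

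Under the assumed 5% FDR and 1–10% true features, the day-specific penalty is material: at n = 60, r rises from 0.355 to 0.45–0.52 and the stated 1.4-fold transcript difference to 1.55–1.7. At 20% true features the n = 60 figures are still 0.42 and 1.50-fold. Because neither the FDR target nor the true share is documented, these are ranges under stated assumptions, not one corrected number. This is a fault in the stated sensitivity; it does not show that the sample is inadequate.

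**What to change.** Restate the detectable r and the transcript fold differences at the error rate the screen will use, for example 5% FDR within each platform and contrast. Show them for 1%, 5%, 10% and 20% true features, at n = 60 for day-specific features and at n = 180 for DOL0 features within a vaccine schedule. Label the alpha 0.05 figures as applying only to one pre-specified test or composite score.

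The cost is recalculation, some wording and a less favourable stated sensitivity. Design and recruitment are unchanged.
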